## 2. Materials and Methods

### 2.1. Study Design

The study is designed as a prospective, multicenter, nonrandomized phase-II trial to compare IMPT with IMRT/VMAT with photons in patients with LACC treated with pelvic +/− para-aortic radiotherapy combined with concurrent chemotherapy with curative intent. During the first phase of the trial, 15 patients will be enrolled in the IMRT/VMAT treatment group. In the second phase of the trial, 15 patients will be enrolled in the IMPT group. Figure 2 provides an overview of the study design.

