### 2.3. Study Objectives

The primary objective of this trial is to investigate whether in clinical practice IMPT can significantly reduce the D_mean_ to the pelvic bones and the mean V_15Gy_ to the bowel compared to that of IMRT/VMAT with photons. Secondary objectives are to compare IMPT with standard of care IMRT/VMAT with respect to dosimetric parameters, clinical outcomes, health-related quality of life, safety, and tolerability. Furthermore, the effect of IMPT and IMRT/VMAT on the local and systemic immune system are evaluated, as measured by the bone marrow activity on MRI scans with Dixon technique and the number and function of circulating leukocytes (myeloid cells and lymphocytes).

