Differences in dosimetric parameters will be analyzed using a linear regression with a correction for the target volume (pelvic common iliac lymph nodes with or without para-aortic lymph nodes). With respect to differences in clinical outcomes between the two groups, the proportion of patients with a complete response at three months after treatment will be compared with a chi-square or fisher exact test. Kaplan–Meier log-rank test will be used for the overall survival, local, pelvic, and distant recurrence-free survival. For the evaluation of patient reported symptoms and QoL, the European Organization for Research and Treatment of Cancer (EORTC)-core (C-30) questionnaire, the CX24 module for cervical cancer, and six additional questions from EN24 module will be used. Outcomes will be described and compared between the two groups. Toxicity will be graded according to the NCI-CTCAE version 5.0 [30]. Lastly, the differences in immune parameters over time will be analyzed with a mixed model analysis of variance including time, chemotherapy and chemotherapy by time as fixed effects and the subjects as random effects. SPSS and R will be used for statistical analysis. A *p*-value < 0.05 will be considered statistically significant. This comparative study is considered successful when both the pelvic bones D_mean_ and mean bowel V_15Gy_ are significantly lower with IMPT than with IMRT/VMAT.

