#### 2.7.5. Chemotherapy

The standard chemotherapy regimen is weekly cisplatin (40 mg/m^2^) for 5 weeks. Reduced chemotherapy dose to 75% per cycle is permitted when the full dose cannot be given.

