## 4. Conclusions

The prospective PROTECT trial investigates the improvement in dose to OAR, especially bowel and bone marrow, and QoL with IMPT compared to that of IMRT/VMAT in patients with LACC undergoing chemoradiation. The safety, tolerability, and short- and long-term outcomes of IMPT are also assessed. Moreover, the bone marrow sparing capability and effects on the local and systemic immune system of these two radiotherapeutic techniques will be evaluated. In this way, the improvement of outcomes with proton therapy for primary treatment of women with LACC can be substantiated.

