**Inclusion Criteria**
Histological diagnosis of LACC; Curative treatment with chemoradiation (with cisplatin or alternatively carboplatin); Aged 18 years or older; WHO performance status 0–1; Indication to include the common iliac region +/− the para-aortic region into the elective clinical target volume of the EBRT; No distant metastasis beyond the para-aortic lymph node chain; Adequate systemic organ function: ∘ Creatinine clearance (>50 cc/min), ∘ Adequate bone marrow function: white blood cells ≥ 3.0 × 10^9^/L, neutrophils ≥ 1.5 × 10^9^/L, platelets ≥ 100 × 10^9^/L.

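### The mixed model stated for the immune parameters has no IMPT versus IMRT/VMAT term, so as written it cannot estimate the technique comparison set as an objective

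*Protocol article*

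**What the plan says.** Section 2.3 of the protocol article states, after the primary and secondary objectives, that "the effect of IMPT and IMRT/VMAT on the local and systemic immune system are evaluated", as measured by bone marrow activity on MRI and by circulating leukocytes. Section 4 repeats the aim: "effects on the local and systemic immune system of these two radiotherapeutic techniques will be evaluated". Section 2.7.6 schedules blood for immune monitoring at six times: baseline, week 3 of treatment, 4, 8 and 12 weeks after treatment, and 12 months after treatment.

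Section 2.6 gives the analysis of immune parameters over time as a "mixed model analysis of variance including time, chemotherapy and chemotherapy by time as fixed effects and the subjects as random effects".

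On chemotherapy, Section 2.1 describes all participants as "treated with pelvic +/− para-aortic radiotherapy combined with concurrent chemotherapy with curative intent". Section 2.2 requires an indication for primary chemoradiation, and Table 1 lists as an inclusion criterion "Curative treatment with chemoradiation (with cisplatin or alternatively carboplatin" (closing bracket omitted). Section 2.7.5 gives a single regimen, "The standard chemotherapy regimen is weekly cisplatin (40 mg/m^2^) for 5 weeks", and adds: "Reduced chemotherapy dose to 75% per cycle is permitted when the full dose cannot be given".

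**The concern.** The factor in the model is not the factor in the objective. The trial compares two radiotherapy techniques, 15 patients each, all with concurrent chemotherapy. The model asks whether immune trajectories differ by chemotherapy and says nothing about technique.

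An analyst who follows the sentence obtains no estimate, interval or p-value for IMPT versus IMRT/VMAT. An analyst who departs from it chooses the model after the data are in. With 15 patients per group and potentially many immune parameters, that choice should be fixed beforehand.

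There is a second difficulty if chemotherapy is taken to mean the dose or number of cycles received. The Introduction and Discussion raise the possibility that less immunosuppression, or IMPT itself, improves treatment tolerance. Dose received could then lie on the path from technique to immune outcome, and adjusting for it could absorb part of the effect sought.

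**Working it through.** The article gives no power or sample size for the immune endpoints, so there is no figure to reproduce. The check is whether the stated fixed effects can carry the technique contrast.

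**Inputs.** 15 patients per group, 30 in all (Section 2.1); 6 blood-sampling times (Section 2.7.6); fixed effects as listed in Section 2.6; chemotherapy given to all (Sections 2.1 and 2.2, Table 1). Neo-adjuvant chemotherapy is an exclusion criterion in Table 1, so it cannot be the intended factor.

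**Columns of the stated model.** Intercept 1, time 6 − 1 = 5, chemotherapy 1, chemotherapy by time 5. Total 1 + 5 + 1 + 5 = 12.

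**Technique parameters needed.** Group 1, group by time 5. Total 6. With baseline as the reference time, the group term is the difference before treatment, and the five interaction terms are the between-technique differences in change from baseline.

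**Rank of the fixed-effect design matrix (30 patients × 6 times = 180 rows).**

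| Model | Columns | Rank |
|---|---|---|
| A. Stated, chemotherapy = yes for everyone | 12 | 6 |
| B. A plus group and group by time | 18 | 12 |
| C. Stated, chemotherapy varying between patients | 12 | 12 |
| D. C plus group and group by time | 18 | 18 |
| E. Time, group, group by time (chemotherapy dropped) | 12 | 12 |

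Models C and D need an assumption, because the article does not say how agent or dose will vary. A two-level patient characteristic was simulated at 30% prevalence.

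**Reading the table.**
- A: the chemotherapy column equals the intercept and the interaction columns equal the time columns. Only 6 parameters are identified, one mean per time point.
- B minus A: rank rises by 12 − 6 = 6, so all six technique parameters lie outside the stated model.
- C: if chemotherapy means agent or reduced dose, its terms can be estimated.
- D minus C: rank again rises by 18 − 12 = 6. The technique parameters are still missing.
- E: replacing the factor gives full rank, and the group effect and all five group-by-time contrasts can be estimated from the planned data.

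**The case against.** **The article is condensed, and its list of terms need not be exhaustive.** The dosimetric sentence in the same section also names only its covariate, target volume, and leaves the obvious group term unsaid. This is the best defence, and it means that one cannot assert that no group term exists in the full protocol or analysis plan. It does not rescue the sentence. Target volume is presented there as a correction, which implies a main comparison. The immune sentence names a factor together with its interaction with time, which is the place of the main comparison. That reads as the wrong factor, not a shortened list.

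**Chemotherapy does vary.** Table 1 allows two agents and Section 2.7.5 allows dose reduction. This stands. A reader might infer that the chemotherapy terms can never be estimated; that holds only for yes/no coding. It does not supply the technique contrast.

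**Chemotherapy is not necessarily a mediator.** This also stands in part. A reader might infer that any chemotherapy variable is post-enrolment and must be excluded. The planned agent is part of the eligibility criterion and can be known at enrolment, so in a nonrandomized comparison it may be a legitimate baseline covariate. The caution applies to dose or cycles received, and even there the article raises better tolerance as a possibility to be assessed, not as an established effect.

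**The sentence may concern only change over time within patients.** Then the analysis would not serve the objective in Sections 2.3 and 4, and the chemotherapy terms would have no evident purpose.

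**The endpoint is not primary.** This is correct and limits the severity.

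**Conclusion.** Wrong as written; should be fixed. Followed as stated, the model gives no estimate of IMPT versus IMRT/VMAT for any immune parameter: none of the six technique parameters is in it, whether chemotherapy is coded yes/no (rank 6 of 12, time only) or as agent or dose (12 of 12, technique still absent). This takes the listed fixed effects as the whole list; no other section of the article adds a group term.

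A reader might go further and conclude that the immune comparison is lost or the trial's conclusion compromised. The article does not support that. The six samples per patient are collected whatever the model, and the contrast can be estimated once the factor is corrected. Success rests only on pelvic bones mean dose and bowel V15Gy, which are analysed by a separate linear regression. No power statement depends on the immune model.

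**What to change.** In Section 2.6, and in the analysis plan if it carries the same wording:

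- State the fixed effects as time, radiotherapy group (IMPT versus IMRT/VMAT) and group by time, with subject as random effect, and name group by time as the between-technique test.
- Preferably add target volume (para-aortic yes/no) as a covariate, as in the dosimetric regression. Each group may contain 7 to 10 para-aortic patients, so the groups can differ by up to 10 − 7 = 3 of 15. This is advisable, not needed to cure the defect.
- Remove chemotherapy and chemotherapy by time as the factor of interest. Planned agent may stay as a baseline covariate. Report cycles or dose received descriptively or in a labelled sensitivity analysis.

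Cost: about one sentence of text, no new data and no change in sample size. It should be made before the immune data are analysed by group.

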### 2.7. Investigation Schedule

#### 2.7.1. Preregistration Evaluation Procedures

The appropriate treatment for each patient is based on interdisciplinary assessment following approved diagnostic procedures and treatment guidelines [4,29]. Staging is based on physical examination, a pelvic MRI scan, a chest CT or radiograph, and an optional total body PET-CT scan. The baseline toxicity and QoL will be evaluated. 

#### 2.7.2. External Beam Radiation Therapy Planning

For external beam radiation therapy, the use of a ‘library of plans’ technique with daily selection of the most appropriate treatment plan using cone beam CT (CBCT) is standard of care in the participating centers [31]. CT planning scans in treatment position with full and empty bladder will be obtained and merged to create an internal target volume (ITV) accounting for movement of the uterus and cervical vault region by variations in bladder and rectal filling. OAR include the rectum, sigmoid, bowel bag, bladder, femoral heads, kidneys, spinal cord, and the whole pelvic bone contour. Dose coverage, planning aims, and hard dose constraints for the OAR will be according to the EMBRACE-II protocol [29]. Since the specific goal in this project is to aim for simultaneous bone marrow and bowel sparing, treatment planning of both IMPT and IMRT/VMAT will be optimized for bone marrow and bowel sparing.

#### 2.7.3. External Beam Radiation Therapy Delivery

EBRT is given to a total dose of 45 Gy in 25 daily fractions of 1.8 Gy in 5 weeks. Involved nodes are boosted using a simultaneous integrated boost (SIB) to reach a total EBRT plus brachytherapy dose of 60 Gy EQD2 to provide high nodal control [32]. CBCT scans or, when available, in-room CT scans are used for daily evaluation of patient positioning and the selection of the most appropriate treatment plan. 

#### 2.7.4. Brachytherapy

Brachytherapy is performed using a high-dose rate (HDR) after loading system to deliver a boost to any residual tumor and the cervix. Brachytherapy dose is (21-) 28 Gy in fractions of 7 Gy specified at 100% isodose around the high-risk CTV, according to the EMBRACE-II prescription protocol. The aim is to reach an equivalent dose in 2 Gy fractions including EBRT (EQD2_D90) of the high-risk CTV between 90–95 Gy, using MRI-guided adaptive brachytherapy [29]. The maximum overall treatment time including EBRT and brachytherapy is 50 days.

#### 2.7.5. Chemotherapy

The standard chemotherapy regimen is weekly cisplatin (40 mg/m^2^) for 5 weeks. Reduced chemotherapy dose to 75% per cycle is permitted when the full dose cannot be given.

#### 2.7.6. Monitoring during Treatment and Follow-Up

In Figure 4, an overview of the timepoints for data collection per patient is shown.

Patients will have an MRI scan with Dixon technique for evaluation of bone marrow activity at baseline, for all brachytherapy purposes, and at 12 weeks and 12 months after treatment. Blood samples will be collected at baseline, week 3 of treatment, and 4, 8, and 12 weeks and 12 months after treatment for immune-monitoring using the same methods described previously by our group [17]. Tumor biopsies will be collected at baseline and at the first brachytherapy session for evaluation of the impact of treatment on the local immune response. QoL questionnaires will be completed at baseline, week 3 of EBRT, at completion of brachytherapy and at 3, 6, 9, and 12 months after treatment.

Four weeks after treatment, the first clinical response assessment will be done. If applicable, hormonal replacement therapy, vaginal dilators, and vaginal estrogens will be prescribed as per standard practice. Tumor and nodal remission will be assessed as complete, uncertain complete, partial, stable, or progressive disease at three months after treatment by gynecological examination and a pelvic MRI scan and/or thoraco-abdominal-pelvic CT scan. When remission is uncertain, imaging will be repeated after 2–3 months and, if applicable, finally histological confirmation will be obtained in case of persistent or recurrent disease.

Thereafter, patients will be followed up at 3-month intervals by the radiation oncologist and gynecologic oncologist during the first few years. At each follow-up visit, tumor recurrence and treatment-related morbidity will be assessed by targeted patient history and physical and pelvic examination. Additional imaging will only be performed in case of symptoms or suspicion of recurrence.

### 2.8. Duration of the Study

The accrual of the patients for IMRT/VMAT is expected to be completed within one year. The subsequent accrual of the patients for the proton therapy group is expected to be completed within 1.5 years. The study ends one year after the last patient completes treatment.

## 3. Discussion

The PROTECT trial is the first prospective clinical trial to compare IMPT with IMRT/VMAT for women with LACC treated with primary chemoradiation. The study is expected to yield a wealth of information on the differences in dose-volume parameters, physician and patient-reported morbidity, and the immune system. Compared to that of IMRT/VMAT, proton therapy is expected to substantially reduce the unwanted exposure of OAR to radiation dose for women with LACC, while maintaining the high level of disease control. Resulting reductions in morbidity have the potential to importantly improve QoL and functioning of cancer survivors. As women with LACC are most often diagnosed in the early decades of their lives, these improvements are of major societal relevance. Moreover, this clinical study creates a unique opportunity to study the effects of both types of radiation therapy on the local and systemic immune response. The bone marrow sparing effect of proton therapy may reduce the considerable immune suppressive impact of the current IMRT/VMAT photon techniques, which may in turn increase the likelihood of safe and effective delivery of additional systemic (immune) therapies. This is especially relevant in patients at high risk of distant metastasis. With the PROTECT trial, the potential of proton therapy for LACC to positively influence the chemoradiation treatment tolerance will be assessed. In the future, IMPT might facilitate treatment intensification, i.e., by the addition of adjuvant immune therapies to the treatment of high-risk patients.

The use of proton beam therapy is increasing. Since proton therapy is more expensive than photon therapy, it is important to identify the (sub)population of each cancer type for whom proton therapy is most cost effective [33]. Several tumor types, including intra-ocular, base-of-skull, low-grade brain tumors, and pediatric cancers, have a standard indication for IMPT in the Netherlands. For other tumor types, including head-and-neck, breast, esophageal and lung cancers, and lymphomas, normal tissue complication probability (NTCP) models are used to select patients who are expected to benefit significantly from proton therapy [34]. Currently, patients with pelvic and gynecological cancers have no indication for proton therapy in the Netherlands. The PROTECT trial will allow for the development and implementation of proton therapy for LACC. Planning studies demonstrated that IMPT could significantly reduce the dose to OAR when compared to that of IMRT/VMAT. This phase-II trial is the next step to evaluate whether these dose differences are feasible in clinical practice. Since the patients included in this study will be the first to undergo IMPT for pelvic cancer in the Netherlands, the safety, tolerability, and short- and long-term outcomes of the technique are also evaluated. Our results will provide essential data to develop indications and guidelines for proton therapy for LACC.

Existing data on outcomes and toxicities of proton therapy in LACC are limited. The earliest studies investigated proton therapy as an alternative to brachytherapy or used older techniques for proton therapy delivery [35,36,37]. Two other studies demonstrated the feasibility of proton therapy for gynecological cancer treatment. A small, prospective single-arm study by Lin et al. evaluated 11 patients with gynecological cancer treated posthysterectomy and showed that pencil beam scanning (PBS) PT was able to reduce the dose to the OAR substantially compared to IMRT plans [26]. Xu et al. demonstrated that PBS PT resulted in significantly lower volumes of exposed bone marrow, small bowel, and bladder when dosimetrically comparing PBS PT with IMRT for endometrial cancer [27]. An ongoing trial is the APROVE study, which is a prospective single-center one-arm study wherein 25 gynecological cancer patients with an indication for postoperative pelvic radiotherapy will be treated with PBS PT [38]. The aim of this study is to explore the advantages of proton therapy in radiotherapy for gynecological cancers. In contrast to the APROVE study, our trial uses a control group to compare IMPT with IMRT/VMAT for women with LACC treated with primary chemoradiation. When the PROTECT trial provides the first data on the potential of IMPT to reduce OAR dose and improve toxicity and QoL for patients with LACC, additional prospective studies with bigger cohorts and longer follow-up time will be needed to verify and substantiate these findings.

## 4. Conclusions

The prospective PROTECT trial investigates the improvement in dose to OAR, especially bowel and bone marrow, and QoL with IMPT compared to that of IMRT/VMAT in patients with LACC undergoing chemoradiation. The safety, tolerability, and short- and long-term outcomes of IMPT are also assessed. Moreover, the bone marrow sparing capability and effects on the local and systemic immune system of these two radiotherapeutic techniques will be evaluated. In this way, the improvement of outcomes with proton therapy for primary treatment of women with LACC can be substantiated.

## Figures and Tables

**Figure 1 cancers-13-05179-f001:**
[figure not shown]
A typical dose distribution for the para-aortic region for IMRT (**left**) and IMPT (**right**) [24].

**Figure 2 cancers-13-05179-f002:**
[figure not shown]
Schematic scheme of PROTECT’s study design. IMRT, intensity-modulated radiation therapy; VMAT, volumetric-modulated arc therapy; IMPT, intensity modulated proton therapy.

**Figure 3 cancers-13-05179-f003:**

Sample size calculation to determine power to detect significant differences in pelvic bones D_mean_ (Gy (**left**) and bowel mean V_15Gy_ (cc) (**right**) when comparing IMPT and IMRT/VMAT.

**Figure 4 cancers-13-05179-f004:**
[figure not shown]
Overview of data collection points per patient enrolled in the PROTECT trial. *, data collection point; EBRT, external beam radiation therapy; W, week; M, month; MRI, magnetic resonance imaging; QoL, quality of life.

**Table 1 cancers-13-05179-t001:** Inclusion and exclusion criteria for participation in the PROTECT trial.

**Inclusion Criteria**
Histological diagnosis of LACC; Curative treatment with chemoradiation (with cisplatin or alternatively carboplatin); Aged 18 years or older; WHO performance status 0–1; Indication to include the common iliac region +/− the para-aortic region into the elective clinical target volume of the EBRT; No distant metastasis beyond the para-aortic lymph node chain; Adequate systemic organ function: ∘ Creatinine clearance (>50 cc/min), ∘ Adequate bone marrow function: white blood cells ≥ 3.0 × 10^9^/L, neutrophils ≥ 1.5 × 10^9^/L, platelets ≥ 100 × 10^9^/L.
**Exclusion Criteria**
Another primary malignancy active or present within the last 5 years; Other severe diseases such as recent myocardial infarction; Previous pelvic or abdominal radiotherapy; Previous major abdominal/pelvic surgery for LACC; Neo-adjuvant chemotherapy treatment; (History of) active primary immunodeficiency or autoimmune disorder; Use of immunosuppressive drugs at baseline.

LACC, locally advanced cervical cancer; WHO, World Health Organization; EBRT, external beam radiation therapy.
